### Blinding and statistical methods

All participating rheumatologists and radiologists will be blinded against the interventions, thus assuring blinded assessment of outcome variables.

The primary endpoint is the progression of radiographic damage after one year compared to baseline (measured by the SHS). Analysis will be performed in three steps to compare the three groups (Pl: placebo group; V10: group starting with 10 mg PRED; and V60: group starting with 60 mg PRED). Primary analysis will be conducted by analysis of covariance (ANCOVA) for V60 versus Pl, using baseline values as covariates and 12-month values as dependent variables. In case of a statistically significant result (α = 0.05), a comparison of V10 versus Pl will be performed (α = 0.05). In case of superiority of V10 versus Pl, a non-inferiority test for V10 versus V60 will be performed (α = 0.025), as is shown in Figure 2. A non-inferiority margin of 1.3 SHS points has been selected.

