## Methods/Design

### Trial design

CORRA is a multicenter, randomized, placebo-controlled, double-blind clinical trial conducted in 30 rheumatology practices in North Rhine-Westphalia, Germany. Most of these practices are members of the RheumaNetz Westfalen-Lippe, a local cooperation of rheumatologists in the eastern part of North Rhine-Westphalia. In total, 450 patients with early active RA will be randomized to receive one of two GC treatments (starting with 10 or 60 mg PRED, tapered down to 5 mg PRED within eight weeks) or placebo, each arm comprising 150 patients. The duration of the intervention is 12 weeks. In parallel, all patients start medication with methotrexate (MTX), at a usual dosage of 15 mg/week. The primary efficacy endpoint is radiographic joint damage after one year compared to baseline. Important secondary endpoints are the percentage of patients in remission, patient global assessment of disease activity, and changes of functional capacity. Safety monitoring is performed.

The study is approved by the local ethic committees Ethik-Kommission der Ärztekammer Westfalen-Lippe und der Medizinischen Fakultät der Westfälischen Wilhelms-Universität Münster (leading ethic committee: 2013-250-f-A), Ethik-Kommission der Ärztekammer Nordrhein, Dusseldorf, and Ethikkommission bei der Ärztekammer Niedersachsen, Hannover. It is registered at the European Union Drug Regulating Authorities (EudraCT: 2012-004074-25), at ClinicalTrials.gov (NCT02000336), and German Clinical Trials Register (DRKS-Nr: DRKS00004774). The principles of good clinical practice will be an essential component of the trial. It will be conducted in accordance with the Declaration of Helsinki. All patients will be required to give written informed consent before inclusion in the study.

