**Table 2 Tab2:** **Scope of study visits and assessments of the CORRA study**

	Physical examination, DAS28, laboratory, safety assessment	Radiographs of hands and feet	Patient global assessment, functional capacity, EQ-5D	DXA lumbar spine and hip
Baseline	+	+	+	(+)
Week 5	+			
Week 9	+			
Week 13	+		+	
Week 25	+		+	(+)
Week 53	+	+	+	

CORRA: Comparison of the efficacy and safety of two starting dosages of prednisolone in early active rheumatoid arthritis, DAS28: Disease Activity Score 28, EQ-5D: EuroQol-5D, DXA: Dual-Energy X-ray Absorptiometry.

Allocation concealment is ensured as the randomization code will not be released until the end of the study. Randomization will be performed using blocks with variable block length according to centre. Quality assurance and monitoring will be performed in 100% of data for the inclusion and exclusion criteria, verification of treatment compliance, primary endpoint, and AE. Other trial data will undergo 100% source data verification for 20% of patients.

The treating rheumatologist will record all AE including serious AE and, if necessary, make treatment adjustments in accordance with the protocol. Serious AE are defined as any adverse reaction resulting in any of the following outcomes: a life-threatening condition or death, a significant or permanent disability, a malignancy, hospitalization or prolongation of hospitalization, a congenital abnormality, or a birth defect.

Supervision of the trial will be performed by an independent data and safety monitoring board (DSMB). In case of unexpected safety concerns the biostatistician of the DSMB will perform an interim analysis. The committee will ensure adherence to protocol and provide the funding organization with information and advice.

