### Sample size

It is assumed that progression of radiographic joint damage as measured by the SHS will be the same for both dosage levels of PRED. For sample size calculation we used data from the BeSt-study [9]. We thus assume an effect of 3.7 and a standard deviation of 7.5. Accounting for a 5% dropout rate, the effect will be 3.5. If 150 patients per group are included, a two sided t-test of superiority (α = 0.05) between one of the PRED groups and the placebo group will give a power of >0.95. Accepting a non-inferiority margin of 1.3 (one third of the known placebo-verum difference) for the difference in progression between the PRED groups, the one sided non-inferiority test in step three (at α = 0.025) will give a power of >0.80, if 149 patients per PRED group are included. The significance level of α = 0.025 was chosen according to the European Medicines Agency guidelines [25]. Thus, the final sample size has been set as 150 patients per group.

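### Randomisation is blocked by centre but the primary ANCOVA names only baseline: if centre is prognostic, the tests are slightly conservative and a little power is forgone, mainly in step three

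*Protocol article*

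**What the plan says.** All references are to the protocol article.

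- **Trial design:** a "clinical trial conducted in 30 rheumatology practices in North Rhine-Westphalia, Germany", with 150 patients in each of three arms.
- **Study medication, randomization, and follow-up (text after Table 2):** "Randomization will be performed using blocks with variable block length according to centre".
- **Blinding and statistical methods:** V60 is compared with placebo by ANCOVA, "using baseline values as covariates and 12-month values as dependent variables". V10 versus placebo and then the non-inferiority test of V10 against V60 follow in sequence.
- **Other adjustments:** the additional analysis of the primary outcome (Secondary outcome parameter) adjusts for methotrexate dose, biologicals and later glucocorticoid dose. The ANCOVAs of secondary outcomes adjust for baseline. Centre appears in neither list.
- **Sample size:** "We thus assume an effect of 3.7 and a standard deviation of 7.5"; "Accounting for a 5% dropout rate, the effect will be 3.5"; "a two sided t-test of superiority (α = 0.05) between one of the PRED groups and the placebo group will give a power of >0.95"; and "the one sided non-inferiority test in step three (at α = 0.025) will give a power of >0.80, if 149 patients per PRED group are included". These are calculations without a centre term. No between-centre variance or intraclass correlation is given.

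**The concern.** Centre is the randomisation stratum. Blocking within a stratum balances the arms inside each practice, so differences between practices largely cancel in the treatment contrast. A model without the stratum still counts those differences as residual noise. The reported standard error then exceeds the true sampling variability, confidence intervals are wider than the design warrants, and the test rejects less often than its nominal level.

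A centre effect is plausible here. The treating rheumatologist may modify the methotrexate dose and decides on later changes of DMARD, and the article itself treats biologicals, methotrexate and later glucocorticoid use as influences on the Sharp score. Prescribing habits by practice could shift one-year SHS.

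What is at stake is efficiency. It matters most in step three, where the confidence limit has to clear a margin of 1.3 points.

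**Working it through.** **Inputs from the article.** 30 centres; 150 per arm, so 450/30 = 15 patients per centre and about 5 per arm per centre. Steps one and two: effect 3.5 (3.7 × 0.95 = 3.515), SD 7.5, two-sided α = 0.05. Step three: margin 1.3, true difference 0, one-sided α = 0.025, 149 per group.

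**Assumption.** ρ is the share of the residual variance, given baseline SHS, that lies between centres. The article gives no value, so the range 0 to 0.10 is shown. The SD is treated as the total residual SD, as in the article's own calculation.

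**The article's own figures first.**
- Steps one and two: SE = 7.5 × √(2/150) = 0.866. Power = Φ((3.5 − 1.96 × 0.866)/0.866) = 0.981. The stated power above 0.95 is reproduced.
- Step three: SE = 7.5 × √(2/149) = 0.869. Power = Φ((1.3 − 1.96 × 0.869)/0.869) = 0.32. The stated power above 0.80 is not reproduced. An SD of about 4.0 gives n = 149 and power 0.801, but the article states no such SD. Step three is therefore shown at both values.

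**Effect of leaving centre out.**
- True SE = reported SE × √(1 − ρ), so the reported SE is too large by the factor 1/√(1 − ρ).
- Actual two-sided type I error = 2 × (1 − Φ(1.96/√(1 − ρ))).
- Power without centre = Φ((d − 1.96 × reported SE)/true SE), where d is the effect or the margin.
- Power with centre: noncentral t with noncentrality d/true SE and 29 fewer degrees of freedom.

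Example, step three at SD 7.5 and ρ = 0.10: true SE = 0.869 × √0.90 = 0.824. Power without centre = Φ((1.3 − 1.703)/0.824) = 0.312. Power with centre = 0.349.

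| ρ (assumed) | SE overstated | Two-sided type I error | Steps 1–2, without → with centre | Step 3, SD 7.5 | Step 3, SD 4.0 |
|---|---|---|---|---|---|
| 0 | 0% | 0.050 | 0.981 → 0.981 | 0.321 → 0.319 | 0.801 → 0.798 |
| 0.02 | 1.0% | 0.048 | 0.982 → 0.983 | 0.320 → 0.325 | 0.803 → 0.806 |
| 0.05 | 2.6% | 0.044 | 0.984 → 0.985 | 0.317 → 0.333 | 0.807 → 0.818 |
| 0.10 | 5.4% | 0.039 | 0.986 → 0.989 | 0.312 → 0.349 | 0.814 → 0.838 |

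Most of the small drop at ρ = 0 comes from moving from a normal to a t calculation: with t throughout, step three at SD 4.0 goes from 0.7985 to 0.7982.

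**Simulation check** (30 centres, assumed permuted blocks of 3 or 6, centre as a fixed effect, 3,000 runs per setting). At ρ = 0.10 with centres of equal expected size, the mean SE without centre was 0.864 against an empirical SD of 0.834, which is 3.6% too large. With very unequal centres it was 0.863 against 0.821, which is 5.1% too large. The gains from adding centre in step three at SD 7.5 were 0.321 → 0.358 and 0.304 → 0.339. With very unequal centres, fixed effects showed no consistent gain at ρ = 0.02. At ρ = 0 they cost up to about 0.6 points (0.798 → 0.792 in step three at SD 4.0).

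**The case against.** **The effect is conditional.** A reader might infer that the standard errors are certainly too large and that power is lost in all three steps. The article does not support that. The effect requires between-centre variance that remains after conditioning on baseline SHS, and no such figure is given. Differences in case mix, with disease duration allowed up to three years, may be partly absorbed by baseline. The practices work to the same treat-to-target and EULAR principles, and most belong to one regional network. All of this stands: ρ could be close to zero.

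**Nothing is lost against the planned power in steps one and two.** The plan's calculation has no centre term. With the total SD held fixed, a prognostic centre raises the unadjusted power there from 0.981 to 0.986 at ρ = 0.10. This also stands. The loss is a gain forgone relative to a better model.

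**Step three.** A reader might also link this point to the low power of step three. That shortfall comes from the SD and margin in the sample size section. At SD 7.5, adding centre moves power from about 0.31 to at most 0.35, so it is a separate matter and lends this one no weight.

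**The full protocol and SAP are not shown.** The wording does not exclude a design factor, and handling of small centres is commonly left to the SAP. This stands in part. However, the article does more than stay silent: it names the covariates of the primary model and lists adjustments for two other sets of analyses, and centre is in none of them. An SAP that added centre would go beyond the published primary model.

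**Conclusion.** The point holds in conditional form and is of low severity. The article states a primary model that omits its own randomisation stratum. If centre explains 2% to 10% of the residual variance, the standard error is overstated by about 1% to 5%, and the two-sided tests run at about 4.8% to 3.9%. For the one-sided step-three test, half of that is about 2.4% to 1.9%. The power forgone is under 0.5 points in steps one and two and about 0.5 to 3.6 points in step three at SD 7.5, or 0.3 to 2.5 points at SD 4.0. If centre explains nothing, there is no effect.

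These sizes rest on the assumed range for ρ, the article's SD used as the residual SD, and near balance of arms within centres. Type I error stays at or below nominal throughout, so the validity of the three-step procedure is not in question.

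**What to change.** Add centre to the primary ANCOVA in steps one to three. A random intercept suits about 15 patients per centre. The alternative is a fixed effect with a prespecified rule for pooling small centres. Settle the choice before unblinding. If the SAP already includes centre, it is enough to confirm that and to bring the description of the primary model into line.

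The change is one phrase and needs no new data. If centre turns out not to be prognostic, the cost is about 0.1 to 0.3 points of power by calculation. The simulated cost of up to about 0.6 points arose with very unequal centres and fixed effects, which is a reason to prefer the random intercept or a pooling rule. No calculation was made for the secondary or repeated-measures models, so the recommendation is limited to the primary analysis.

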### Participants

The 2010 RA classification criteria established by the American College of Rheumatology/EULAR collaborative initiative will be used in this trial to enable the early diagnosis of RA [16]. In general, most patients enrolled in this trial will be seen by a rheumatologist early in the course of their disease. To meet the circumstances of routine rheumatology care where patients are sometimes seen with a delay of many months, patients with a disease duration of up to three years may be enrolled. In general, patients will be MTX naïve (MTX pretreatment of four weeks or less is allowed).

To outweigh the risks of MTX and GC treatment, RA activity must be moderate or high as measured by a Disease Activity Score 28 (DAS28) of >4. The DAS28 score is a compound score comprising the number of tender joints (out of 28), swollen joints (out of 28), the erythrocyte sedimentation rate (ESR, after 1 hour), and the patient’s assessment of disease activity. The range of the score is 0 (no activity) to 10 (maximum disease activity) [17]. In patients with a pain disorder such as fibromyalgia, the DAS28 score may be unduly elevated because of the high number of tender joints. To ensure a sufficient amount of inflammatory disease activity, the number of swollen joints should be three or more for a patient to be enrolled in the trial.

Key exclusion criteria will ensure that no patients with very high risks for GC or MTX toxicity will participate in the trial. The exclusion criteria are in accordance with standard rheumatological decision-making and therefore do not promote undue patient selection for this study.

To avoid an inappropriate risk of MTX toxicity, it is mandatory to exclude patients with severe liver disease, active hepatitis B or C viral infection, renal disease (creatinine clearance <30 ml/minute), clinically relevant hematological disease, relevant immunodeficiency including HIV infection, clinically significant pulmonary fibrosis, complicated gastric or duodenal ulcer, a history of malignant melanoma, pregnancy or planned pregnancy, or severe infections within the previous six weeks before study participation.

Patients with uncontrolled diabetes mellitus, arterial hypertension, or intraocular pressure should not receive GC treatment and are therefore excluded as well. On general grounds, non-compliant patients and patients outside the range of 18 to 80 years will not be allowed to participate.

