**Table 1 Tab1:** **Schedule of the prednisolone dosage (mg/day) of the three study arms of the CORRA study**

Day	Placebo	V10	V60
1 - 7	0	10	60
8 - 14	0	10	40
15 - 21	0	10	25
22 - 28	0	10	20
29 - 35	0	7,5	15
36 - 42	0	7,5	10
43 - 49	0	7,5	7,5
50 - 56	0	7,5	7,5
57 - 84	0	5	5

CORRA: Comparison of the efficacy and safety of two starting dosages of prednisolone in early active rheumatoid arthritis, PRED: prednisolone, V10: group starting with 10 mg PRED; V60: group starting with 60 mg PRED.

In parallel, all patients will start MTX medication at a usual dosage of 15 mg/week (modifications may be made by the rheumatologist, for example due to minor renal insufficiency or age).

Patients are seen every four weeks within the first three months. In case of lack of efficacy, the MTX dose will be increased to 20 mg/week and further up to 25 mg/week, after four or eight weeks, respectively. In the further course of the study, a change of DMARD medication according to the EULAR recommendations [14] is allowed in case of lack of efficacy and/or intolerable side effects. These decisions are made by the treating rheumatologist based on the treat–to-target paradigm for RA [11].

Study visits will take place at baseline and after 4, 8, 12, 24, and 52 weeks (Figure 1). Physical examination, determination of DAS28, and safety measures including lab examinations will be performed at every visit. Radiographs of hands and feet will be done at baseline and after one year. Functional assessments including the EuroQol-5D [18], Patient Health Questionnaire-2 [19], and physical functioning questionnaire Hannover (FFbH) [20] are planned at baseline and after 12, 24, and 52 weeks. Dual-Energy X-ray Absorptiometry (DXA) of the lumbar spine and hip at baseline and after 24 weeks is planned in case of at least one of the following: age >60 years for men, >50 years for women, current smoker, history of non-traumatic fracture, parental history of hip fracture (Table 2).

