### Primary outcome parameter

One of the best evaluated and relevant outcome measures in the assessment of RA is the radiographic joint damage as measured by the van der Heijde modification of the Sharp score (SHS) [21]. This score reflects the structural damage caused by the inflammatory joint disease.

Radiographic joint damage, as assessed by the SHS or other scoring systems, correlates with physical function [22], employment status [23], and mortality [24]. The effects discussed in the literature are comparable to the effects assumed for this study. According to the ‘window of opportunity’ concept, reduced radiological damage early in the course of RA leads to a beneficial modification of the long-term outcome. Therefore, the primary outcome parameter will be the progression of radiographic joint damage after one year compared to baseline measured by the SHS.

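### Optional improvement: the primary ANCOVA names no baseline disease-activity covariate, so a modest and nearly free gain in precision is forgone

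*Protocol article*

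**What the plan says.** Under Blinding and statistical methods, the primary comparison of the 60 mg group with placebo is an ANCOVA "using baseline values as covariates and 12-month values as dependent variables". Since the endpoint is one-year SHS progression, the baseline value is most naturally baseline SHS. No other covariate is named. ANCOVA is explicit only for this first step; step two is called a comparison and step three a non-inferiority test.

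On the role of inflammation, the section Primary outcome parameter says of the SHS: "This score reflects the structural damage caused by the inflammatory joint disease". Under Participants, "RA activity must be moderate or high as measured by a Disease Activity Score 28 (DAS28) of >4", and at least three swollen joints are asked for. The same section describes the score's make-up: "The DAS28 score is a compound score comprising the number of tender joints (out of 28), swollen joints (out of 28), the erythrocyte sedimentation rate", together with the patient's own assessment.

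On availability, the text after Table 1 states: "Physical examination, determination of DAS28, and safety measures including lab examinations will be performed at every visit". Table 2 confirms this for baseline.

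Two further points bear on the question. Randomisation is blocked by centre, not by disease activity. The only other adjusted analysis described for the primary outcome (end of Secondary outcome parameter) uses variables that arise after randomisation: mean methotrexate dose, use of biologicals and mean glucocorticoid dose in weeks 13 to 52.

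**The concern.** Patients enter with anything from moderate to very high activity, because the entry rule sets a floor and no ceiling. If activity at randomisation predicts one-year progression beyond baseline SHS, a model without it leaves predictable variation in the error term. Every confidence interval is then somewhat wider than the collected data require.

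This would matter most where precision is scarce. Step three is one such place. Steps one and two are another if the true effect is smaller than planned, and the Discussion itself considers that prednisolone may no longer have a major disease-modifying role under treat-to-target care. The procedure is hierarchical, so failure at step one or two also closes step three.

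**Working it through.** **Inputs from the Sample size section.** "We thus assume an effect of 3.7 and a standard deviation of 7.5". After 5% dropout the effect is taken as 3.5. There are 150 patients per group, with two-sided α = 0.05 for superiority. For non-inferiority the margin is 1.3, the true difference between the prednisolone groups is 0, one-sided α = 0.025, and 149 per group are stated.

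**Assumed input.** R² is the share of residual variance that baseline activity explains beyond baseline SHS. The documents give no value, so 5%, 10% and 15% are shown. SD 7.5 is treated as the residual SD of the stated model.

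**The plan's own figures first.**
- Superiority: SE = 7.5 × √(2/150) = 0.866. The noncentral t with effect 3.5 gives power 0.981, in agreement with the stated value above 0.95.
- Non-inferiority: with margin 1.3, SD 7.5 and 149 per group, power is 0.32, not above 0.80. At SD 7.5, 523 per group would be needed for 0.80. The stated 149 is recovered only with an SD of about 4.0, which the article does not give.

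**Effect of adding the covariate.** The residual SD becomes 7.5 × √(1 − R²). The SE falls by 1 − √(1 − R²), and the equivalent gain in sample size is 1/(1 − R²) − 1.

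| Assumed R² | 0 | 5% | 10% | 15% |
|---|---|---|---|---|
| SE, 150 per arm | 0.866 | 0.844 | 0.822 | 0.798 |
| Reduction in SE | – | 2.5% | 5.1% | 7.8% |
| Equivalent extra patients | – | 5% | 11% | 18% |
| Superiority power, effect 3.5 | 0.981 | 0.985 | 0.989 | 0.992 |
| Superiority power, effect 3.5/2 = 1.75 | 0.52 | 0.54 | 0.56 | 0.59 |
| Step-three power, SD 7.5, 149 per arm | 0.32 | 0.33 | 0.35 | 0.37 |
| Step-three power, SD about 4.0, 149 per arm | 0.80 | 0.82 | 0.84 | 0.86 |

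The effect of 1.75 is an illustration of a smaller true effect, not a figure from the article. The last row uses the back-solved SD.

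**Could the covariate repair step three?** Going from SD 7.5 to about 4.0 requires R² = 1 − (4.005/7.5)² = 0.71. Nothing in the documents suggests that baseline activity explains that much.

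**The case against.** The strongest reply is that nothing here is wrong. ANCOVA on the baseline value of the outcome is a valid primary analysis. In a randomised comparison, leaving out a further prognostic covariate biases nothing and does not inflate type I error, and the standard error already allows for chance imbalance in activity. Activity is not a stratification factor that the model is obliged to carry. All of this stands, and it limits the point to one of efficiency.

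The gain also rests on an R² with no source, and the documents give reasons why it could be small. The entry rules cut off the lower end of the activity range. Treat-to-target escalation may also weaken the link between baseline activity and one-year damage if more active patients are escalated more. This stands too, and is why a range is shown and no size is claimed as known.

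The article condenses a fuller protocol, which may list more covariates. That is possible, but the article does state a model, and the suggestion is directed at that statement.

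A reader might infer that the plan itself names DAS28, ESR or swollen joints as the cause of radiographic damage. It does not: it names the inflammatory joint disease, and these are measures of that disease. No section calls them predictors of SHS progression.

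Finally, the change is not quite a single phrase, because of the radiograph replacement rule in steps one and two. That is correct, and the fix has to cover it.

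**Conclusion.** The point holds as an optional, nearly free improvement. The stated model forgoes a covariate that is available in every patient and is plausibly related to the outcome. If that covariate explains 5 to 15% of residual variance, the SE falls by about 2.5 to 8%. At the planned effect this hardly matters for steps one and two. At half that effect it is worth 2 to 7 percentage points of power.

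Two stronger readings are tempting and are not supported. The first is that precision is materially lost in all three steps: superiority power is already about 0.98 at the planned effect, and any loss depends on an R² that the documents do not give. The second is that adjustment would rescue step three: at SD 7.5 power stays at 0.33 to 0.37. The mismatch between the stated SD, margin, group size and power in step three is a separate and larger matter that this covariate does not resolve.

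**What to change.** Under Blinding and statistical methods, specify for all three steps an ANCOVA of 12-month SHS on treatment, baseline SHS and baseline DAS28, with DAS28 as one linear term fixed before unblinding. Naming the single score, and not a choice between it and its components, leaves nothing to decide later. The effect measure (mean difference in SHS points) and the margin of 1.3 stay as they are. The wording would also make the model explicit for steps two and three.

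Add one sentence to the replacement rule for steps one and two: when a placebo donor's pair of films replaces missing radiographs, the donor's baseline DAS28 enters the model with the donor's baseline SHS, so that covariates and outcome come from the same patient. Step three excludes missing values and needs no such rule.

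The cost is one degree of freedom and that extra sentence. No new data are needed, since DAS28 must be known to establish eligibility.
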